**Fig. 3 Fig3:**
[figure not shown]
Position of the tapes

**Fig. 4 Fig4:**
[figure not shown]
Position of the gyroscopes

##### Hip abductor strength

Hip abductor strength (continuous scale) is measured using the ‘make-technique’ with a microfet2™ handheld dynamometer (HHD) (Hoggan Scientific LLC., Salt Lake City, Utah, United States) with the patient lying in supine position. A fixation-belt is used to stabilise the pelvis and prevent sliding. The HHD is applied 22 cm distal of the most prominent aspect of the greater trochanter. For each strength test, following a warm-up of one submaximal contraction, all patients perform three maximal trials for 3 to 5 s with a 1-min rest interval. The maximum of three valid trials is used. The torque value (Nm) of the hip musculature is normalised by body weight in kilograms (kg), resulting in a torque value in Nm/kg. This hip abductor strength test is a modification from the test described by Pua et al. [49]. A reproducibility study is now ongoing.

##### Prosthetic use

The prosthetic use score (continuous scale: 0–100 points) of the Dutch version of the questionnaire for persons with a transfemoral amputation (Q-TFA) is used to assess the patient-reported prosthesis wearing time [50]. A higher score represents a longer wearing time.

##### Back pain

A single question (ordinal scale) ‘*Did you experience back pain within the previous month?*’ with three response alternatives; ‘no’, ‘yes, with episodes’ and ‘yes, chronic (daily)’ is used to assess back pain frequency [46].

##### Stump pain

Post-operative stump pain (continuous scale) is assessed during follow-up using the Numeric Rating Scale (NRS: 0–10) [51]. Pain location (nominal scale) is assessed for descriptive purposes with seven response alternatives: ‘no location’, ‘soft tissue stoma’, ‘distal side stump’, ‘ventral side stump’, ‘inguinal area’, ‘greater trochanter area’ or ‘other’.

#### Level of activity

##### Mobility level

The mobility level is assessed using three patient-reported outcome measures (ordinal scales: a-c) and one physical performance measurement (continuous scale: d): a) the Medicare Functional Classification Level (MFC-level) [52], also known as ‘k-levels’ (0–4) in which ‘k0’ represents a non-ambulatory person and ‘k4’ a high-level prosthesis user; b) the Special Interest Group in Amputee Medicine Workgroup Amputation and Prosthetics (SIGAM WAP) mobility score (class A-F) [53] where ‘class A’ represents an abandoned prosthesis user and ‘class F’ a prosthesis user with a normal gait without aids; c) a question concerning the use of aids in daily life, both for indoor use and outdoor use, with a 5-point likert scale answer; ‘wheelchair-bound’, ‘walking frame/rollator’, ‘two crutches/canes’, ‘one crutch/cane’, ‘none’; d) the timed up and go (TUG) using a standard arm chair (seat height 46 cm, arm height 67 cm) and a 3 m walking course marked by a pylon, representing the level of physical mobility [54]. The fastest attempt (in seconds) of three TUGs is noted as final time score.

##### Walking ability

Walking ability is evaluated using two measurements (continuous scales): a) a self-paced 6-minute walking test (6MWT). Patients walk six minutes as fast as they can without encouragement, on a 10 m course marked by two pylons representing the submaximal level of functional capacity [55, 56]. Total walking distance will be recorded in metres and walking speed will be calculated in metres per second as an indicator of gait performance [57, 58]; b) a single question: ‘*How far can you walk in one go in everyday life?*’ representing a patient-reported estimation of the walking distance in daily life in metres [46].

#### Level of health-related quality of life

The Q-TFA global score (continuous scales: 0–100 points) is used to assess HRQoL and is a summary of three items: perception of function, problems with the current prosthesis and the perception of the current overall amputation situation [29, 50]. A higher score reflects a better HRQoL. All three items are scored on a 5-point likert scale. For patients not using a prosthesis only the single overall question (ordinal scale) is used; ‘*How would you summarize your overall situation as an amputee?*’, with five response alternatives; ‘extremely poor’, ‘poor’, ‘average’, ‘good’ or ‘extremely good’.

#### Level of satisfaction

##### Prosthesis comfort

To assess the satisfaction of the patient in regards to their prosthesis, including the socket or bone-anchored prosthesis aspect, the Prosthesis Comfort Score (PCS) [46] is used. The PCS (continuous scales) is a single question ‘*How satisfied are you with your current prosthesis on a scale of 0 to 10, where 0 is not satisfied and 10 extremely satisfied?*’.

##### BAP satisfaction

Global perceived effect of BAP (ordinal scale) is assessed within the post-operative follow-up using a single question ‘*Would you, with your current knowledge, choose for a BAP again?*’ with five response alternatives; ‘strongly disagree’, ‘disagree’, ‘neutral’, ‘agree’ or ‘strongly agree’.

### Statistical analysis

All outcomes will be analysed non-stratified. Additionally, we will stratify for level of amputation and for baseline wheelchair-boundedness when applicable. The size of the subgroups will determine whether statistical tests will be used to analyse the outcomes of the subgroups, or if only descriptives will be presented. All analyses will be performed using SPSS v23 (SPSS Inc., Chicago, Illinois, United States). In all cases, two sided *p*-values <0.05 will be considered to be statistically significant.

#### Descriptive statistics

Categorical data will be presented as exact numbers. Percentages will be calculated for the various levels. For the continuous data, means and standard deviations will be calculated for normally distributed variables. For data not-normally distributed median and inter-quartile ranges will be used. Missing data will be analysed and imputation techniques will be used where necessary.

#### Aim 1: longitudinal statistics

Change over time in level of function, activity, HRQoL and satisfaction will be analysed for all continuous outcomes (coronal plane kinematics, hip abductor strength, prosthetic use, mobility level, walking ability, HRQL and prosthesis comfort) and for one categorical outcome (back pain). Generalised estimating equations (GEE) for repeated measurements with an exchangeable correlation structure will be used [59–61]. Back pain will be dichotomised for this analysis into ‘no back pain’ and ‘back pain’ (representing the classes ‘yes, with episodes’ and ‘yes, chronic (daily)’). Continuous outcomes (mean change) and the dichotomised outcome (odds ratio) will be presented with 95% confidence intervals.

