### Sample size

We will not draw a sample, but aim to include the entire population, which started in May 2014. We expect to have little non-responders as all assessments are part of usual care. This expectation is supported by the fact that we had no non-responders since the start of this study. Based on the average number of surgeries in the Netherlands during the year 2014 and 2015 we expect that 18 patients will be included each year [44]. For our first aim, investigating change over time, we will present the first interim analyses of this growing cohort when we have a minimum of 40 patients at the following time points: one-, two- and five-year follow-up. Press-fit BAP surgery started in the Netherlands in 2009. Between 2009 and 2014, 42 patients received a BAP. Thus at the time of our first interim analyses (mid of 2017) the total Dutch population with a minimum follow-up of one-year will include 82 patients [44]. Although, the sample size of 40 patients appears to be small, the study will have gathered longitudinal data (with a minimum follow-up of one-year) in 49% of the total Dutch population of patients with a press-fit BAP. We expect that this is sufficient to be able to generalise the results to the Dutch population eligible for a press-fit BAP. Of the patients included in this study to date, none have dropped out. We also do not anticipate any high drop-out rates for the remainder of the study as the assessments are part of usual care.

We will use the rule-of-thumb for prediction modelling with multiple factors and assume that we need ten cases per predictor [45]. The various continuous outcomes of interest have a different number of potential predictors (Additional file 1) ranging from three to seven variables. A minimum of 30 subjects are needed for prosthetic use, 40 subjects for HRQoL, 50 subjects for walking ability and prosthesis comfort, 60 subjects for coronal plane kinematics, and 70 subjects for stump pain. Based on these numbers we expect to complete the inclusion of patients for this study around May 2018.

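### For continuous outcomes, GEE at 40 patients or ten patients per predictor needs a small-sample variance and reference; with the usual uncorrected sandwich, nominal 5% tests run at about 6% to 10%

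*Protocol article*

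**What the plan says.** Under Aim 1: longitudinal statistics, change in the continuous outcomes and in dichotomised back pain is analysed by GEE: "Generalised estimating equations (GEE) for repeated measurements with an exchangeable correlation structure will be used". Mean changes and odds ratios get 95% confidence intervals. The sections on Aims 2 to 4 also use GEE. The Statistical analysis section sets the level: "In all cases, two sided *p*-values <0.05 will be considered to be statistically significant".

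The Sample size section gives the minimum numbers. For the first aim, "we will present the first interim analyses of this growing cohort when we have a minimum of 40 patients at the following time points" of one, two and five years. For prediction models the authors "assume that we need ten cases per predictor", with candidate sets "ranging from three to seven variables". The sizes that follow from this rule are listed by outcome: "A minimum of 30 subjects are needed for prosthetic use, 40 subjects for HRQoL, 50 subjects for walking ability and prosthesis comfort, 60 subjects" (this last figure being the one for gait kinematics); the model of stump pain has a floor of 70. The prediction section removes predictors with p above 0.15 on a likelihood-ratio test.

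Results are also stratified by amputation level and by baseline wheelchair use. On testing within strata: "The size of the subgroups will determine whether statistical tests will be used to analyse the outcomes of the subgroups". No threshold is given.

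**The concern.** GEE inference is justified for a large number of independent patients. The sandwich variance that normally accompanies GEE is biased downwards when patients are few. A normal or chi-square reference also ignores the uncertainty in that variance. Both effects make p-values too small and intervals too narrow.

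The plan's minimum sizes do not address this. The 40 for Aim 1 is a convenience minimum, and the prediction sizes come from a rule of thumb about model complexity. At stake are the coverage of the reported intervals and the number of noise predictors reported as useful.

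**Working it through.** **The plan's own figures.** Ten per predictor with 3 to 7 predictors gives 30, 40, 50, 60 and 70, as stated. For Aim 1, 42 + 40 = 82 and 40/82 = 48.8%, given as 49%. There is no power calculation to reproduce.

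**Single change, continuous outcome.** Assume complete data, visit as a factor and normal differences. The uncorrected sandwich standard error is then the standard deviation of the differences with divisor n, over √n. The true size is therefore P(|t(n−1)| > 1.96·√((n−1)/n)).
- n = 40: 1.96·√(39/40) = 1.935, so the size is 6.0%. The correct critical value is 2.023, so the interval has 1.935/2.023 = 95.7% of its proper width.
- n = 20 and n = 10 (assumed stratum sizes): 7.1% and 9.6%, with widths of 91.3% and 82.2%.

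**Joint test of time with q degrees of freedom.** The robust Wald statistic is Hotelling's T² times n/(n−1). Its size is P(F(q, n−q) > c·(n−q)/(n·q)), where c is the 95% chi-square point on q degrees of freedom. At n = 40:
- q = 2: 5.991·38/80 = 2.846, size 7.1%
- q = 3: 7.815·37/120 = 2.410, size 8.2%
- q = 4 (all five visits): 9.488·36/160 = 2.135, size 9.7%

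**Predictors at ten patients each.** With balanced visits and patient-level predictors, exchangeable GEE reduces to least squares on patient means, and its sandwich to the uncorrected heteroscedasticity-robust variance. Simulated size for one null predictor at nominal 5%, with 20,000 runs per setting:

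| Patients / predictors | Sandwich, z: normal predictor | Sandwich, z: binary, 20% | Sandwich, z: binary, 10% | Model-based, t: normal predictor |
|---|---|---|---|---|
| 30 / 3 | 10.2% | 12.4% | 19.5% | 5.0% |
| 40 / 4 | 9.2% | 11.3% | 17.2% | 4.8% |
| 50 / 5 | 8.9% | 9.9% | 15.0% | 5.0% |
| 60 / 6 | 8.0% | 9.1% | 13.3% | 4.9% |
| 70 / 7 | 8.2% | 8.6% | 12.8% | 4.9% |

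The prevalences are assumptions; the article gives none. A Mancl-DeRouen variance with a t reference brings these sizes to 4.1–4.4% (normal), 4.3–5.4% (20%) and 6.0–8.5% (10%).

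**Removal rule read as a Gaussian likelihood-ratio test on patient means.** A predictor stays if n·ln(1 + t²/(n−p−1)) exceeds 2.072, the chi-square point for 0.15. With n = 30 and p = 3, |t| must exceed √(26·(e^(2.072/30) − 1)) = 1.364, so a noise predictor stays 18.4% of the time. At n = 70 and p = 7 the figure is 17.7%. Nominal is 15%.

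**Model-based errors when correlation decays.** The visits are at 0, 0.5, 1, 2 and 5 years. Suppose the correlation over a gap of d years is r^d. Exchangeable GEE uses the average of the ten pairwise correlations, r̄. A five-year change then has model-based variance proportional to 1 − r̄ but true variance proportional to 1 − r⁵. The large-sample size is P(|Z| > 1.96·√((1−r̄)/(1−r⁵))).
- r = 0.80: r̄ = 0.636, r⁵ = 0.328, ratio of standard errors 0.736, size 14.9%
- r = 0.95: r̄ = 0.892, r⁵ = 0.774, ratio 0.692, size 17.5%

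**Back pain odds ratio.** A simulated robust logit GEE (two visits, assumed latent correlation 0.5) at n = 40 gives 5.4%, 5.2% and 4.1% at prevalences of 0.52, 0.68 and 0.84. These span the 52–84% quoted in the Discussion.

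**The case against.** The strongest objection is that the article names no sandwich variance, no Wald test and no reference distribution. A condensed article may leave these to an analysis plan that is not shown. That stands: a reader might infer that the plan prescribes robust z-tests that are too liberal, and the text does not say so. The point has to be conditional. However, model-based inference held close to 5% only because the simulated data were exchangeable. The article fixes that structure over five years, and a sandwich is the usual protection if it is wrong.

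Other stronger readings also fail.
- A reader might apply robust Wald sizes to the removal rule and conclude that noise predictors stay about 19% to 22% of the time. The article specifies a likelihood-ratio test. Under a Gaussian reading the excess is small. GEE has no full likelihood, so which test is meant is unclear, but that is a separate matter.
- A reader might extend the point to every GEE analysis. Back pain is not liberal at 40, and at n = 10 it is conservative (3.8% or less).
- A reader might take 30 to 70 as the sizes at analysis. They are minima, and 18 patients a year over four years gives about 72. With 70 patients and 3 to 6 predictors, the uncorrected sandwich still gives 7.5% to 8.0%.
- A reader might assume that strata of 10 or 20 will be tested. The plan allows them to be described only, and gives no stratum sizes.

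**Conclusion.** The point holds in conditional form, for continuous outcomes. With an uncorrected sandwich and a normal or chi-square reference, a single change at 40 patients is only slightly liberal (6.0%). A joint test of time has size 7.1% to 9.7%. Normally distributed predictors at the plan's minima have size about 8% to 10%, and uncommon binary categories more. Model-based errors remove the problem if the exchangeable structure is right, but can reach about 15% to 18% for five-year change if correlation decays at an assumed 0.80 to 0.95 per year. The removal rule, read as a likelihood-ratio test, keeps noise about 18% of the time against 15%.

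These figures assume normal residuals and complete data; missing visits and skewness were not modelled. The joint test of time is a natural use of the model but is not stated in the article. The defect is moderate and is best settled before the analyses are run.

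**What to change.** For continuous outcomes in Aims 1 to 3, use a linear mixed model with visit as a factor, a covariance not forced to be exchangeable, and Satterthwaite or Kenward-Roger degrees of freedom. An unstructured covariance over five visits has 5·6/2 = 15 parameters, so name a simpler fallback in which correlation falls with time. This model also supplies a real likelihood for the planned test, fitted by maximum likelihood when fixed effects are compared; the small excess over 15% remains unless an F test is used.

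Alternatively, keep GEE with a bias-corrected sandwich such as Mancl-DeRouen and a t or F reference. This still leaves some excess for categories of about 10% prevalence.

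Apply the same choice to any stratum that is tested, and state the minimum stratum size for testing. Confirm that the planned software offers the chosen option.

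The cost is a change of wording and procedure, with no new data. Intervals become slightly wider and fewer predictors are retained.

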Aim 1: to describe the change in the level of function, activity, HRQoL and satisfaction in patients with a lower extremity amputation after receiving a press-fit BAP at short-term (six-months and one-year), mid-term (two-years) and long-term (five-years) follow-up in comparison to baseline. We hypothesise that coronal plane kinematics symmetry, hip abductor strength, prosthetic use, mobility level, walking ability, HRQoL and prosthesis comfort will improve over time and that the frequency of back pain will decrease over time.

Aim 2: to examine potential predictors for the change of coronal plane kinematics, prosthetic use, walking ability, HRQoL and prosthesis comfort over time: outcomes that are the main reason why patients choose a BAP The potential predictors which will be included in the analysis are: demographic data, patient characteristics, baseline level of function, baseline level of activity and baseline level of satisfaction (Additional file 1).

Aim 3: to examine predictors for the level of stump pain at short-term, mid-term and long-term follow-up (Additional file 1). In our clinic we see that stump pain after BAP surgery negatively influences outcomes on the level of function, activity, HRQoL and satisfaction. However, we do not have insight in the level of stump pain at follow-up and knowledge concerning predictors for stump pain is absent.

Aim 4: to examine potential mechanisms for changes in back pain at short-term, mid-term and long-term follow-up. We hypothesise that an increase of coronal plane kinematics symmetry will be a possible determinant for a decrease in back pain (Fig. 1). We also hypothesise that stump pain will act as moderator and hip abductor strength will act as mediator.

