## Discussion

All assessments included in this study are part of usual care. This is, in our opinion, an advantage because the risk of missing data and loss to follow-up is expected to be low. The Netherlands is a relative small country, resulting in small logistical challenges. This differs from other countries where bone-anchored prosthesis surgery is performed (e.g., Sweden, Germany, Australia). There are a few limitations to our study design. 1) A disadvantage of data collection during usual care is that it may lead to measurement bias. Measurements may have to be performed by a different rater in unforeseen circumstances and the rater is also the treating physiotherapist. Furthermore, the used measurement instruments are rarely gold standard tools. In order to limit measurement bias, we standardised the measuring procedures as described in this study protocol, limited the maximum number of raters to two across all follow-ups and trained the raters. Three of our measurement instruments (Dartfish® angle measurement, Valedo®Motion angle measurement and hip abductor strength test) are developed specifically for this study. Therefore, no information concerning their psychometric properties are readily available, but a reproducibility study concerning these measurements is now ongoing. 2) To increase the compatibility of our study results with other available literature, we have chosen to use the Q-TFA to evaluate prosthesis wearing time (prosthetic use score) and HRQoL (global score) in all patients, regardless of their level of amputation. The Q-TFA is specifically developed for patients with a transfemoral amputation, but the constructs we investigate in this study do not involve specific questions related to the level of amputation that could influence the validity of the results. Furthermore, the Q-TFA is widely used in studies which evaluate bone-anchored prosthesis use, both in patients with a transtibial as with a transfemoral amputation [40]. 3) Walking ability is investigated by patient-reported estimation of the walking distance in daily life. This may be less accurate than using a pedometer or activity tracker, but the results are clinically relevant. Patients’ may overestimate or underestimate, yet this is likely to happen structurally and therefore will not lead to biased results. 4) We have not included a measure investigating back pain intensity. Although back pain frequency is included, the method is too robust to identify more subtle changes, such as back pain intensity, that may also be an important clinical measure of treatment. For example, patients may still experience back pain but to a much lesser degree than before. The prevalence of back pain is high (52–84%) in patients with a lower extremity amputation using a socket prosthesis [21, 62–64]. This study will explore if back pain is a common secondary disability as well in the BAP population and we will examine potential mechanisms for change of back pain over time. Knowledge of these mechanisms can influence the content of rehabilitation programme and future studies may include questions regards to back pain intensity.

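### Back pain frequency is recorded on three levels but tested only as none versus any, so a move from daily to episodic pain counts as no change in Aim 1; the mobility measure to be modelled also needs naming.

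*Protocol article*

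**What the plan says.** **Back pain.** The section Back pain describes a single question "with three response alternatives" (none, episodic, daily) that "is used to assess back pain frequency". The Background, under Aim 1, hypothesises that "the frequency of back pain will decrease over time". The section Aim 1: longitudinal statistics then states "Back pain will be dichotomised for this analysis into" two classes, with episodic and daily merged, and reports an odds ratio with a 95% confidence interval from a GEE. Descriptive statistics promises counts and percentages for categorical data. Aim 4: causal model for change of back pain also uses GEE but does not state how back pain is coded.

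**Mobility.** The section Mobility level lists "three patient-reported outcome measures (ordinal scales: a-c") and one continuous performance test, the timed up and go (TUG). The Aim 1 analysis section places mobility level among "all continuous outcomes (coronal plane kinematics, hip abductor strength, prosthetic use, mobility level" and others), to be reported as a mean change. It does not say which of the four measures is meant.

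**The concern.** The Aim 1 hypothesis is about frequency, and the item grades frequency. The planned coding keeps the step from none to some pain and discards the step from episodic to daily. If BAP surgery mainly turns daily pain into episodic pain, Aim 1 would report an odds ratio near 1 although frequency had fallen. The cohort is small: the interim analysis needs at least 40 patients, and 18 per year over the four years from May 2014 to May 2018 gives 18 × 4 = 72. The article gives no reason for the dichotomisation.

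The mobility entry raises a separate question of consistency. If it means the whole domain, three scales that the article itself calls ordinal would be summarised by a mean change. If it means the TUG alone, the other three have no stated Aim 1 model, although mobility level is hypothesised to improve.

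**Working it through.** **1. The article's own figures.** Sample size gives ten cases per predictor: 10 × 3, 4, 5, 6, 7 = 30, 40, 50, 60, 70, as stated. It also gives 40/(42 + 40) = 40/82 = 48.8%, stated as 49%. Both reproduce, and neither concerns back pain. There is no power figure for back pain to check.

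**2. What follows from the coding alone.** If half of the patients with daily pain become episodic and nothing else changes, the proportion with any pain is the same before and after, so the yes/no odds ratio is exactly 1.

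**3. Size under a uniform shift (illustration).** From the article: two-sided 0.05, n = 40 and 72, and baseline prevalence of 52–84% in socket users (Discussion), with 68% as the midpoint. Assumed, because the article gives none of them: a latent normal severity x at baseline; follow-up y = 0.5x + √(1 − 0.5²)·e − 0.5; cut-points at z(1 − prevalence) and z(1 − prevalence × daily share), with a daily share of 30% or 50%. Each run compares a paired t-test on the yes/no change with one on the 0/1/2 score change, baseline against one follow-up, 20,000 runs. Ranges are over the two daily shares.

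| Prevalence | n=40 yes/no | n=40 three-level | n=72 yes/no | n=72 three-level |
|---|---|---|---|---|
| 52% | 0.54 | 0.64–0.65 | 0.82–0.83 | 0.88–0.89 |
| 68% | 0.54 | 0.71 | 0.82–0.83 | 0.92 |
| 84% | 0.43 | 0.71–0.72 | 0.72 | 0.92–0.93 |

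Smallest and largest losses: at n=40, 0.644 − 0.543 = 0.10 and 0.723 − 0.434 = 0.29; at n=72, 0.884 − 0.821 = 0.06 and 0.931 − 0.723 = 0.21.

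**4. Size by where patients move (illustration).** Half of baseline pain is taken as daily, and in every pattern 10% of pain-free patients become episodic.
- A, daily to episodic: 50% of daily become episodic; 10% of episodic become pain-free.
- B, both steps: of episodic, 30% become pain-free and 5% daily; of daily, 10% become pain-free and 30% episodic.
- C, episodic to none: of episodic, 40% become pain-free and 5% daily; 10% of daily become episodic.
- D, opposing moves: as C, but 25% of episodic become daily.

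Entries are power, yes/no versus three-level score, at prevalence 52 / 68 / 84%.

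| Pattern | n=40 | n=72 |
|---|---|---|
| A | 0.05 v 0.31 / 0.03 v 0.64 / 0.05 v 0.91 | 0.10 v 0.54 / 0.04 v 0.91 / 0.13 v 0.995 |
| B | 0.14 v 0.35 / 0.36 v 0.67 / 0.69 v 0.90 | 0.21 v 0.64 / 0.58 v 0.92 / 0.92 v 0.99 |
| C | 0.13 v 0.15 / 0.35 v 0.36 / 0.68 v 0.62 | 0.21 v 0.26 / 0.60 v 0.62 / 0.91 v 0.89 |
| D | 0.14 v 0.05 / 0.36 v 0.09 / 0.69 v 0.16 | 0.21 v 0.06 / 0.59 v 0.14 / 0.92 v 0.27 |

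**5. Does one common odds ratio suffice?** Take pattern A at 68% prevalence. Daily pain goes from 0.34 to 0.34 × 0.5 = 0.17, so its odds ratio is (0.17/0.83)/(0.34/0.66) = 0.40. Any pain goes from 0.68 to 0.68 + 0.032 − 0.034 = 0.678, so its odds ratio is (0.678/0.322)/(0.68/0.32) = 0.99. The two cut-points differ sharply, so proportional odds fails in the very pattern where the yes/no coding does worst.

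**The case against.** The best case for the plan is that any-versus-none is a legitimate target. It is openly stated, including in the Abstract, and it fits the Discussion, which frames the question partly as prevalence. The percentages by level would show a fall in daily pain. The power figures rest on an assumed shift, correlation and daily share. They use two time points and an equally spaced score in place of a repeated-measures cumulative-logit model. In pattern A the yes/no effect is close to zero by construction, and in pattern D the single score does worse than the yes/no coding.

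All of this stands as a limit on size, and it is a reason to keep the yes/no odds ratio. It does not remove the mismatch: the Aim 1 hypothesis is about frequency, and percentages carry neither a test nor an interval.

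Four stronger readings are tempting, and the document does not support them.
- *The article treats ordinal mobility scales as continuous.* It labels them ordinal, and the Aim 1 entry can be read as the TUG alone. No power loss has been shown for mobility.
- *Aim 4 inherits the fault.* The dichotomisation is stated for the Aim 1 analysis; the Aim 4 section gives no coding.
- *The coding removes the improvement that the authors say they fear missing.* Their stated limitation concerns pain intensity, which a three-level frequency item would not recover.
- *Three levels always give more power.* Patterns C and D show otherwise.

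**Conclusion.** The point holds for back pain in Aim 1. A daily-to-episodic move is a fall in frequency as hypothesised, and the only planned test and interval cannot register it. That conclusion follows from the coding and needs no assumption.

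The size is not fixed by the document. Under the assumed 0.5 SD uniform shift and correlation 0.5, the loss is about 6 to 21 power points at n=72 and 10 to 29 at n=40. It is nearly total if improvement is daily to episodic, and almost nil if it is episodic to none. The planned odds ratio remains valid for any-versus-none, so this is an improvement that should be made rather than a fatal flaw. For Aim 4 and for mobility, what is established is an unstated coding and an unnamed instrument.

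**What to change.** - **Aim 1, back pain:** analyse the three levels with a cumulative-logit GEE (independence working correlation, robust standard errors). Report odds ratios with 95% confidence intervals for both cut-points, any versus none and daily versus not daily. The first is the planned yes/no odds ratio and stays. Where the two differ, interpret them separately rather than through one common odds ratio.
- **Aim 4:** state which coding of back pain is used.
- **Mobility:** reconcile the Mobility level and Aim 1 analysis sections. Name the TUG as the continuous measure if that is what is meant, and analyse MFC level, SIGAM class and walking-aid use as ordinal outcomes rather than by mean change.

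No new data are needed. The cost is analysis wording, one extra estimate for back pain, the ordinal models for mobility, and a proportional-odds assumption that showing both cut-points makes visible.
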